### **Objective and Overview of the Study**

to conduct a pilot study to improve insulin sensitivity, prevent weight gain and reduce visceral adiposity in African-American, Hispanic, South Asian, and other high risk populations of normoglycemic, hyperinsulinemic women with midlife weight gain. Enhance the Metabolic Profile of Women with Insulin Resistance (EMPOWIR) will compare three treatment protocols in a randomized, double-blind, clinical trial and optional, post-treatment surveillance analysis.

The objective of the study is to compare the effect of carbohydrate modified diet alone and in combination with metformin (MF) and Avandamet® (metformin plus rosiglitazone (RSG)) on insulin parameters in a wide range of ethnically and economically diverse non-diabetic women (aged 35-55) who meet study selection criteria seen at three academic medical centers: The Hispanic Center of Excellence and The Menopause Research and Treatment Center at Albert Einstein College of Medicine/Montefiore Hospital; The Diabetes Center of Excellence at The University of Tennessee; and The Center for Diabetes and Endocrine Care at New York Medical College/Westchester Medical Center and their affiliated practices. All women will receive the calorie-reduced, carbohydrate modified (sugar restricted, low glycemic index) diet based on large servings of vegetables, fruits, lowfat proteins and dairy products and limited refined carbohydrates and treats. Devised 30 years ago and field-tested in more than a thousand patients in the past decade, this dietary program integrates scientific findings and recommendations from numerous current research studies.

A 3-arm trial will be conducted in a final study population of 75 normoglycemic hyperinsulinemic women (glucose-mediated AUC-insulin >100mU/ml) randomized (Phase 1) to an initial 6-month treatment of study diet, with placebo, metformin, or Avandamet®. Subjects initially randomized to placebo arm will be reassigned after 6 months to one of the two active treatment arms (Phase 2).

Initial funding will be used to develop a core program to facilitate additional research at

[figure not shown]

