| 
Study Design
          | 
Overview
<small>Please see attached Study Flow Chart</small>
 
Chart review of patients at the 3 study Centers and their affiliated General Medical and Gynecology practices and public announcements will be used to identify non-diabetic women who meet selection criteria who will be invited to participate in the study. After obtaining consent, and additional screening for suitability, 80 patients will undergo glucose tolerance testing and additional tests to determine if they meet study inclusion and exclusion criteria. Following a 1-month lead-in phase, an initial study population of 75 women from 3 clinical sites will be randomized to placebo (diet and lifestyle modification) or one of two active study treatment arms for a 6-month study (Phase 1); patients in the diet plus placebo group will then be crossed over to one of the two active study arms for a 2nd six months (Phase 2).
 |
| 
Inclusion / Exclusion
 | 
Inclusion Criteria
 
 
1. Healthy, non-diabetic women with "≥20 pound weight gain since their twenties"
 
2. Age: 35-55
 
3. Peri-menopausal ( FSH ≥25 on day 2-3 of cycle) or postmenopausal status
 
4. Body Mass Index (BMI) 25-35 kg/m^2
 
5. Either:             
 
(a). a single blood pressure recording ≥135/85 or the use of blood pressure medication
 
OR
 
(b) HDL≤50mg/dl or triglycerides ≥150 mg/dl or the use of lipid modifying medication
 
 
 
7. Area-under-the-curve (AUC-)insulin level ≥100μU/ml along with normal fasting (≤100 mg/dl) & postprandial (≤200 mg/dl) glucose determinations following a 75-gram standard oral glucose tolerance test.
 
 
Exclusion Criteria
                                                             |

[figure not shown]

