|--------------------------------------------------------------------------------------------------------|--------------------------------------------------------------------------------------------------------------------------------------------------------------------------------------------------------------------------------------------------------------------------------------------------------------------------------------------------------------------------------------------------------------------------------------------------------------------------------------------------------------------------------------------------------------------------------------------------------------------------------------------------------------------------------------|
| Number of Patients                                                                                     | Total enrollment 75-85 (approx. 20 per site) to capture 60 patients completing the study                                                                                                                                                                                                                                                                                                                                                                                                                                                                                                                                                                                             |
| Projected Enrollment Timeline (proposed start date, proposed finish date, anticipated enrollment rate) | 
Please see attached timeline
 
Projected start date: Sept 1, 2006
 
Projected study completion date: August 30, 2008 (without optional phase)
 
Time-table assumptions:
 
The investigators anticipate a rapid study start-up phase due to:
 
 
a. general ease of enrollment of obesity studies
 
b. investigators' access to large and diverse patient populations in their individual practices and the community
 
c. availability of field tested patient education materials and study instruments
 
d. the availability of nursing and nutrition staff with broad
 
 |

[figure not shown]

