| Study Endpoints/
Objectives                    | 
The study objective is to compare the effects of metformin, and Avandamet® on markers of insulin resistance – fasting, peak (1-hour) and AUC-insulin, and HOMA-R, and body fat distribution in hyperinsulinemic, peri- and post-menopausal women with progressive weight gain (Syndrome W) prior to the onset of overt glycemic abnormalities or full-blown Metabolic Syndrome.
 
The primary outcome variables will be 1-year change in fasting and 1-hour insulin (as noted below.)
                                                                                                                                                                                                                                                                                                                                                                                                                                                                                                                                              |

|                                                                                |                                                                                                                                                                                                                                                                                                                                                                                                                                                       |
|--------------------------------------------------------------------------------|-------------------------------------------------------------------------------------------------------------------------------------------------------------------------------------------------------------------------------------------------------------------------------------------------------------------------------------------------------------------------------------------------------------------------------------------------------|

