| Outcome Parameters / Analytical Endpoints | 
The primary outcome variables are change from baseline in fasting and one-hour insulin at 1 year. Secondary outcome measures are 6 and 12 month change from baseline in body weight, CT scan-determined visceral adipose tissue other fat compartments, and relevant ratio's; total and multimeric adiponectin; and other cardiovascular risk and inflammatory markers, including lipids, c-reactive protein, TNF-<math>\alpha</math>, leptin, ghrelin, and resistin; and IGF-1 and IGF-binding proteins.
                                                                                                                                                                                                                                                                                                                                                                                                                                                                                                                                                                                                                        |
| Statistical Analysis Plan                 | 
Power Calculations and Assumptions
 
Three power calculations were performed incorporating the significance levels and sample size of TZD-based interventions in recently reported studies and comparator trials. A initial sample size of 25 per group is a realistic estimate and is based on the following assumptions:
 
 
1. Placebo treatment even with intensive dietary intervention (which will not be provided after the lead-in phase of EMPOWIR) has low rates of weight loss and high drop out rates at 6 and 12 months of study follow-up in the majority of published studies
 
2. data from observational and population based studies show annual weight gain in women in the study age range and BMI category
 
3. Metformin has a large treatment effect in hyperinsulinemic women and, in combination with hypocaloric carbohydrate modified diet, reduced fasting insulin by 25-40% and 1-hour (peak) insulin by 50% in our preliminary data. (with a mean body weight change 12.5% at 1-year).
 
4. Enrollment goals assume 10% drop out during Phase 2
 
 |

[figure not shown]

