#### Statistical Plan

Mean, median, range and distribution of all baseline study variables will be determined (SPSS (13.0); site differences will be assessed using an Analysis of Variance (ANOVA). All primary and secondary outcome variables will be evaluated using an intention-to-treat analysis with a last observation carried forward (LOCF) for missing data, Paired t-tests will be used to calculate baseline changes in insulin parameters, body weight, BMI, cardiovascular risk factors, and related serum markers (adiponectin, leptin, ghrelin, resistin, C-reactive protein and other inflammatory markers, vitamin D and IGF-binding proteins at 6 and 12 months. Non-parametric measures will be used for comparison of group mean changes at 6 and 12 months. Statistical models will be used to calculate the primary (crude, non-adjusted) treatment effect of the respective study arms and for covariate adjustment by age, initial BMI category and menopausal status,

[figure not shown]

|  |                 |
|--|-----------------|
|  | and study site. |
|--|-----------------|

Publication / Presentation Plan:

Following the analysis of baseline data, abstracts will be submitted for presentation at annual meetings, including The Endocrine Society, The ADA, The American College of Cardiology, NAASO (The National Association for The Advancement of the Study of Obesity, NAMS, (The North American Society for Menopause). Publications will be prepared and submitted at regular intervals, following the collation of baseline data, and the completion of each study phase. A final summary manuscript will be submitted within 6 months of the study completion.

Estimated Study Budget/Requested Support (per patient cost, study medication, other supplies):

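### Publication is tied to the end of each phase, so the 6-month comparison can be analysed and submitted up to 6 months before the last 1-year primary measurement, with no stated shield for investigators or sites

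*Protocol*

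**What the plan says.** The Publication / Presentation Plan, which follows the Statistical Plan, sets the publication trigger: "Publications will be prepared and submitted at regular intervals, following the collation of baseline data, and the completion of each study phase". It then adds a separate last report: "A final summary manuscript will be submitted within 6 months of the study completion". Meeting abstracts are mentioned only in connection with the baseline analysis.

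The rest of the protocol fixes what that trigger means in time:

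- **Blinding.** Under Objective and Overview of the Study, EMPOWIR "will compare three treatment protocols in a randomized, double-blind, clinical trial".
- **Phases.** Under Study Design, Phase 1 is the 6-month randomised comparison of placebo and two active arms. In Phase 2, months 6 to 12, "patients in the diet plus placebo group will then be crossed over to one of the two active study arms".
- **Primary outcome.** Under Outcome Parameters / Analytical Endpoints, the primary variables "are change from baseline in fasting and one-hour insulin at 1 year".
- **6-month data on the same variables.** Under Study Variables, insulin response curves are taken at baseline, 6 and 12 months. The Statistical Plan compares the groups' mean changes at both 6 and 12 months.

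The protocol does not say who runs or sees the 6-month comparison, or that it waits for the last 12-month visit.

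**The concern.** The plan does more than stay silent on interim access. It states a rule that starts a paper when Phase 1 closes, while the data that decide the trial are still being collected. Whoever prepares that paper would see comparative results on fasting and 1-hour insulin, the primary variables, half-way to the primary time point. In a small three-centre study, those people may well be the ones who counsel and follow the women.

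Insulin is measured in a laboratory, but it responds to diet, adherence and staying in the study. Staff who know which group did better at 6 months could advise or encourage the remaining women differently. Women who hear of it could leave or slacken.

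Missing data add to this. The Statistical Plan carries the last observation forward, and the protocol schedules no insulin curve between 6 and 12 months. If that rule is applied to a woman who leaves during Phase 2, her 6-month value, already analysed for the Phase 1 paper, stands in for her 1-year primary value.

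**Working it through.** The plan gives no figure for this overlap, so there is none to reproduce. The check is one of timing.

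**Inputs from the protocol**

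- Study start 1 September 2006 and completion 30 August 2008, about 24 months (Projected Enrollment Timeline).
- Lead-in of 1 month, Phase 1 of 6 months, Phase 2 of 6 months (Study Design).
- 75 women randomised (Study Design).

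**Assumptions**

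- Accrual length E is not stated; the protocol refers to an attached timeline that is not shown. The upper limit follows from the dates: 24 − 1 − 12 = 11 months. I show E from 6 to 11 months.
- Women are randomised evenly over E, and none drops out.
- Phase 1 is complete when the last woman reaches month 6.

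**Step 1: the gap.** Counting from the first randomisation, Phase 1 closes at E + 6 and the last 12-month measurement falls at E + 12. The gap is (E + 12) − (E + 6) = 6 months, whatever E is.

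**Step 2: who is still in Phase 2.** At a lag of L months after Phase 1 closes, the time is E + 6 + L. A woman randomised at time u has not reached month 12 if u > E + L − 6. With even accrual the share still in Phase 2 is

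share = min(1, (6 − L)/E) for L < 6, and 0 for L ≥ 6.

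| Accrual E | L = 0 | L = 1 | L = 2 | L = 3 | L = 6 |
|---|---|---|---|---|---|
| 6 months | 6/6 = 100% | 5/6 = 83% | 4/6 = 67% | 3/6 = 50% | 0% |
| 9 months | 6/9 = 67% | 5/9 = 56% | 4/9 = 44% | 3/9 = 33% | 0% |
| 11 months | 6/11 = 55% | 5/11 = 45% | 4/11 = 36% | 3/11 = 27% | 0% |

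At E = 11, that is 0.545 × 75 = 41 women when Phase 1 closes and 0.273 × 75 = 20 women three months later. Accrual faster than 6 months gives 100% at L = 0 and higher shares at L = 3 (100% at E = 3).

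**Step 3: when a majority remains.** The share equals one half at L = 6 − E/2. That is 3 months at E = 6, 1.5 months at E = 9 and 0.5 months at E = 11.

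**Step 4: who already has the primary value.** When Phase 1 closes, 1 − 6/E of the women have had their 12-month measurement: none at E = 6, 33% at E = 9 and 45% at E = 11.

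**Step 5: is the Phase 1 paper a comparison by arm?** The plan lists baseline publications, phase-completion publications and a final manuscript as separate items. A paper on completion of Phase 1 is therefore neither the baseline paper nor the final report. What Phase 1 adds is the 6-month outcome data, for which a group comparison is planned. It is also the only placebo-controlled period. That the paper reports by arm is a strong inference, but the protocol does not say so.

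**The case against.** A reader might infer that Phase 1 results by arm will be public while most women are still in Phase 2 and before any 1-year outcome is measured, so that the second half becomes an open-label continuation. The documents do not support that reading, for these reasons:

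- **Submission is not appearance.** The plan speaks of preparing and submitting, and gives no date of release. A majority remains in Phase 2 only for a short lag. The one writing interval in the plan is 6 months, for the final manuscript. If the Phase 1 paper took as long, its submission would coincide with the last 12-month visit.
- **Not every primary value is outstanding.** If accrual exceeds 6 months, some women have already had their 12-month measurement.
- **Abstracts are linked to baseline data.** No Phase 1 abstract is specified.
- **Group means need not break the blind.** Randomisation and drug distribution sit with the study pharmacist (Drug Dose). A group comparison can be shown without revealing anyone's allocation. In Phase 2 every woman is on an active arm by design, and which of the two can stay masked.
- **The outcome is a laboratory value,** so biased assessment is limited. No size can be put on any effect through adherence or drop-out.
- **Access rules often sit in an analysis plan or operating procedures,** and none is shown here.

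All of this stands against the stronger reading. It does not remove the point. The exposure arises when the data are analysed and the paper is written, which comes before submission and any journal delay. A document on access may exist, but it would have to work against a trigger that the protocol itself sets before the primary data are complete.

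**Conclusion.** The concern holds in limited form. The publication rule allows the 6-month comparison of the primary variables, presumably by arm, to be analysed and submitted up to 6 months before the last 1-year measurement, and nothing in the protocol shields investigators or sites from it.

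The 6-month gap follows from the design alone. The shares of women affected rest on even accrual over 6 to 11 months and no drop-out: 100% to 55% when Phase 1 closes, 50% to 27% three months later, none at six months. These figures count women exposed to a possible influence. They do not measure bias in the result, which cannot be estimated from the documents.

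This is a cheap improvement, not a flaw that invalidates the 1-year analysis.

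**What to change.** Amend the Publication / Presentation Plan in three respects:

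- Before the last 12-month visit, present only baseline data pooled over the arms.
- Keep Phase 1 results by arm from investigators, site staff and participants until the 12-month data are locked.
- Then report the Phase 1 results together with the 1-year results.

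The cost is a sentence or two in the protocol and a delay of up to about 6 months for the Phase 1 paper. Sample size, visits and analysis do not change.

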**Please see attached**

Funding requested from any other source? No ☒ Yes ☐ If yes, give details:

Additional funding from Public Health sectors will be requested after initiation of EMPOWIR.

[figure not shown]

